### *2.2 STUDY DESIGN*

Bridge will be implemented in four cities, in Kazakhstan: Almaty, Shymkent, Temirtau & Karaganda. Due to their geographical proximity of Temirtau and Karaganda, and overlapping administration of HIV clinics they will be considered as one “site” for intervention roll out. In month 16, we will use computer software to sequentially randomly assign the three sites six months prior to implementing BRIDGE in months 22, 28 and 34.

We opted for a stepped wedge trial over a cluster RCT for ethical reasons so that all clusters will eventually receive the intervention as well as to avoid contamination and to be able to control for exogenous time specific effects as discussed earlier. The unit under experimental control will be a city, with the timing of roll-out of BRIDGE in each of the study’s cities—Almaty, Shymkent Karaganda, and Temirtau—to be randomly assigned. Since the cities are geographically disparate (with the exception of Karaganda and Temirtau, which is why we will consider them as a single study site) the likelihood of participant contamination is minimal.

The stepped wedge approach represents a scientific alternative to the randomized control trial (RCT) by providing a valid counterfactual to evaluate the impact of BRIDGE compared to the TP Standard of Care. This roll out design also more closely resembles the method of implementing BRIDGE in a real-world setting. The use of multiple groups and our data analytic plan will allow us to control for exogenous time-specific effects, such as introducing new HIV initiatives or funding cuts and minimizes contamination as all TP sites in a city will receive BRIDGE at the same time. More importantly, this design addresses important ethical considerations of communities by ensuring that all TP sites will eventually receive BRIDGE, which is a potentially lifesaving intervention.

The following figure describes the stepped-wedge rollout of Bridge in the four cities (with Karaganda & Temirtau combined as one study site):

Figure 2: Stepped Wedge Design

[figure not shown]

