Analysis of Program data: Formal hypothesis testing based on program data will test for differences in outcome measures obtained during the pre-intervention period (i.e., time points before BRIDGE is implemented in a city) versus periods when BRIDGE is implemented. We will employ permutation tests (a.k.a. “randomization tests”) for significance testing because of concerns that the distribution of measures may not be approximated well by a small sample size (i.e.,  $N=24$  TPs). In experimentally controlled trials with small sample sizes, permutation tests have been shown to be superior to parametric tests. As a heuristic and non-parametric approach, permutation testing more accurately estimates the nominal type I error rate for cluster randomized clinical trials with small sample sizes and with measures that may not be normally distributed compared to candidate parametric procedures. Strong hypothesis testing in this manner involves permuting the BRIDGE implementation status of each time point; since the time period “assignment” (pre-implementation vs. BRIDGE) is allocated based on city, permutations will account for clustering by city (i.e., a permutation for TPs in the same city will all be assigned the same implementation status for that time point). Not only does this conservatively account for shared variance that might be present due to being located in the same city, statistical efficiency can be improved by clustered permutation testing. For inference, the test statistic (difference in means) observed based on actual period assignments is compared vis-à-vis the distribution of test statistics using permuted assignments, with the proportion of permuted test statistics greater than the actual observed taken as the one-sided or half of the two-sided p-value. With program measures collected quarterly over 42 months, the number of clustered permutations with 3 study sites (4 cities) is 38,416, allowing testing of statistical significance with  $\alpha < .0001$ . If we permute all 24 TPs independently, tests of significance can be performed with much lower  $\alpha$ . We will conduct both permutation tests with sites permuted independently as well as clustered permutations by city and report the result with the more conservative p-value. Hypothesis testing for Aims 1 and 2—i.e., estimating the effectiveness of the intervention—will involve

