## **CLIENT ENROLLMENT**

BRIDGE trust points are asked to enroll as many PWID clients as possible in the AppSheet system over the course of the study. “Enrollment” means that the process is explained to PWID clients, they agree to take part (as data is de-identified and void of PII or PHI identifiers, we are requesting a waiver of consent for enrolling AppSheet participants in this portion of the study (as discussed in the main protocol), and they receive an ID card with a unique ID in the form of a barcode (detailed below). In discussing the system with their clients, trust point nurses should raise the following points:

- This system is an innovative and simple way of tracking trust point clients that is being implemented at this trust point
- The system is created and monitored by a research study which is interested in how often trust point clients receive services and which services they receive
- Clients will be assigned a random ID number. The nurse is the only person who can connect this number to their UIC code (the code by which clients are registered at the trust point - see below)
- Clients should hold on to their ID card and present it every time they come to the trust point to receive needles/syringes or testing, or every time they go to the AIDS Center for any reason
- If they lose their ID card, the nurse can replace it; they will need to come back to the trust point and provide their UIC number again.

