### Formal hypothesis testing:

Hypothesis testing draws on data from the Google app-based data collection system. The primary test for these hypotheses will be based on patient visits to NSPs, compared at the site (NSP) level. This test will utilize a repeated measures approach and will examine differences in outcome measures obtained during the time points before Bridge is implemented in a city (pre-implementation) versus time points that follow the initiation of Bridge intervention implementation (implementation) in the city. We will employ permutation tests (a.k.a. “randomization tests”) for significance testing because of concerns that the distribution of measures may not be approximated well by a small sample size (e.g.,  $N = 24$  NSPs). Hypothesis testing in this manner involves permuting the Bridge implementation status of each time point; since the time period “assignment” (pre-implementation vs. Bridge intervention implementation) is allocated based on city, permutations will account for clustering by city (i.e., a permutation for NSPs in the same city will all be assigned the same implementation status for that time point). Not only does this conservatively account for shared variance that might be present due to being located in the same city, statistical efficiency can be improved by clustered permutation testing. For inference, the test statistic (difference in means) observed based on actual period assignments is compared vis-à-vis the distribution of test statistics using permuted assignments, with the proportion of permuted test

statistics greater than the actual observed taken as the one-sided or half of the two-sided p value.

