This data requires an analytic approach that accommodates for the non-independence in measures arising from two sources: (1) correlations due to repeated measures with the same NSP and (2) correlations due to NSPs operating in the same city. Hypothesis testing will rely on Generalized Linear Mixed Models (GLMM) and Generalized Estimating Equations (GEE) as recommended for stepped-wedge trials. GLMM is exceedingly flexible and powerful but may not be robust to violations of normality assumptions, which will be examined using various descriptive statistics and further can exhibit difficulties in convergence in some cases. GEE is more robust; however, GEE assumes that missing data are missing completely at random while GLMM assumes that data are missing at random. The exact choice will be informed by the results from analyses that shed insight into the extent that various assumptions hold or are violated (e.g., attrition analyses, parameterization fits). In either case, sandwich estimators for variance will be used which are robust to misspecification of the correlation structure. We will use a link function that can properly model the outcome variable as a function of measurement unit or distribution (e.g., logit for binary outcomes, Poisson or Negative Binomial for count and/or rare outcomes).

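### The stated effect measure is an unadjusted post-minus-pre difference in means; no stated analysis contains a calendar-time term, so trend and AppSheet growth enter the estimated BRIDGE effect

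*Combined protocol and SAP*

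**What the plan says.** Section 2.4 (Analysis of Program data) and the Data Analysis Plan for Primary Study Aim (Formal hypothesis testing) describe the same test. It contrasts "time points before Bridge is implemented in a city (pre-implementation) versus time points that follow the initiation of Bridge intervention implementation", and "the test statistic (difference in means) observed based on actual period assignments is compared" with the values obtained under permuted assignments. City enters through the rule that all trust points (TPs) in a city share a status at each time point.

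The permutation set is described in two ways. The Data Analysis Plan says: "Hypothesis testing in this manner involves permuting the Bridge implementation status of each time point". Section 2.4 says: "With program measures collected quarterly over 42 months", "the number of clustered permutations with 3 study sites (4 cities) is 38,416".

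The last paragraph of the Data Analysis Plan adds GLMM and GEE. The sources of non-independence it lists are "1) correlations due to repeated measures with the same NSP and (2) correlations due to NSPs operating in the same city". It lists no fixed effects and does not say whether the model or the permutation test is primary.

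Section 2.2 states that "our data analytic plan will allow us to control for exogenous time-specific effects".

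The outcome data come from AppSheet, which begins in November 2016 (month 13). Under Client Enrollment, Appendix A says: "BRIDGE trust points are asked to enroll as many PWID clients as possible in the AppSheet system over the course of the study". The hypothesis concerns increased numbers attending, tested and linked.

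**The concern.** In a stepped wedge, implementation always follows control within a site, so exposure and calendar time move together. The staggered start can separate the two, but an estimate does so only if it compares sites within the same period. A pooled difference in means does not. Anything that rises across all sites during the study is added to the reported effect.

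One upward drift is built into the measurement. A client is counted only after receiving an AppSheet ID, and no IDs exist before month 13. Early quarters are mostly pre-implementation quarters, so low early capture pulls the pre-implementation counts down. What is at stake is the size of the primary effect on attendance, testing and linkage and, depending on how labels are permuted, its p-value.

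**Working it through.** **Inputs from the documents.** Quarterly measures over 42 months, so 14 quarters (Section 2.4). Data start in month 13 (Appendix A). Three sites start in months 22, 28 and 34 (Section 2.2), that is, quarters 4, 6 and 8. There are 24 TPs, 8 per site (Section 3.7). Ramp speed, trend size and variance components are not given and are assumed where marked.

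**1. The plan's own figure.** 14 crossover positions for each of 4 cities give 14^4 = 38,416, exactly the stated count. Three sites would give 14^3 = 2,744. The count thus implies one crossover per city, with Karaganda and Temirtau moving separately, although Section 2.2 rolls them out as one site.

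**2. Calendar gap.**
- Pre site-quarters: 3 + 5 + 7 = 15. Post: 11 + 9 + 7 = 27.
- Mean pre quarter: (6 + 15 + 28)/15 = 49/15 = 3.27.
- Mean post quarter: (3 × 105 − 49)/27 = 266/27 = 9.85.
- Gap: 6.59 quarters, about 20 months.

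With no BRIDGE effect and a common slope b per quarter, the crude difference is 6.59b in all six site orders. Assumed growth of 1%, 2% or 5% of the first-quarter level per quarter gives a spurious relative increase of 6%, 13% or 30%.

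**3. Concurrent control.** Only in quarters 4 to 7 have some sites started and others not. They hold 1 + 1 + 2 + 2 = 6 post site-quarters; the other 21 of 27 have no concurrent control.

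**4. AppSheet ramp (assumed shapes, no BRIDGE effect).** With capture 1 − exp(−t/τ), mean capture is 0.726 pre and 0.981 post for τ = 2 (ratio 1.35), and 0.515 and 0.890 for τ = 4 (ratio 1.73). A linear ramp to full capture over 4 quarters gives 100/70 = 1.43.

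**5. Adjusted coefficient.** With site and quarter fixed effects, the spurious effect is 0 for every common trend, ramp and fixed site level tried. The treatment sum of squares is 33/14 + 45/14 + 49/14 = 9.07 after site, and 2.10 after site and quarter. The SE ratio is √(9.07/2.10) ≈ 2.1, at equal residual variance.

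**6. Type I error of the permutation test with the crude statistic.** Simulated with no BRIDGE effect: 500 to 1,000 trials, 999 permutations. Assumed SDs are 1 for TP-quarter, 0.5 for city and 0.3 for city-quarter. The nominal level is two-sided .05.

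| Permutation set | Linear trend | Ramps |
|---|---|---|
| Status shuffled by time point (Data Analysis Plan wording) | 61% at 0.05 SD per quarter, 99% at 0.1 SD | 8% to 100% |
| One crossover per city (implied by 38,416) | 0.3% to 6%, slopes up to 0.2 SD | 0% to 11% (one-sided up to 34%) |
| Six actual site orders | no distortion | no distortion |

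In the last row a common trend or ramp adds the same constant to every order, so the ranking is unchanged. The smallest p is 1/3! = 1/6 one-sided, or 1/3 under the plan's doubling rule.

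**The case against.** The strongest reply has four parts.

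- **The reference distribution.** The difference in means is used only by comparison with permuted assignments. If those assignments also place implementation after control, they inherit most of the trend. This stands for the p-value. With one crossover per city (each after quarter 1 to 13), a noise-free linear trend gives a one-sided p of about 0.105, not significant. A reader might infer that an ineffective programme would be declared effective; the documents support that only if status is shuffled quarter by quarter, which the count of 38,416 contradicts. Nor can one say that the test makes no use of the staggered start. The reply does not rescue the effect estimate.
- **The model.** Section 2.4 refers to a population-level effect from statistical models, and the Data Analysis Plan invokes GLMM/GEE as recommended for this design. No fixed effect is listed, not even the intervention, so the silence about period is not an exclusion. That is fair, but random effects and sandwich variances deal with correlation, not confounding by time. An analyst could follow the text in full and omit time.
- **The ramp.** Its speed is assumed. Appendix A surveys every attending client, and enrolment starts nine months before the first roll-out. Percentages with numerator and denominator both from AppSheet are less exposed. This limits the size but leaves the counts named in the hypothesis exposed.
- **City mix.** The sites' shares of pre quarters are 20/33/47% and of post quarters 41/33/26%. A reader might infer that city differences are credited to BRIDGE. They are not, systematically: the order is randomised and the error averages zero over the six orders. The prevalence range of 7% to 21% is not a range of outcome levels and gives no magnitude.

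**Conclusion.** The concern holds for the effect estimate. No stated analysis delivers the time control promised in Section 2.2, and the one effect measure that is written out carries 6.6 times any common quarterly trend. That multiplier follows from the documents' schedule and does not depend on the order drawn. The AppSheet inflation of about 1.35 to 1.73 rests on the assumed ramp and applies to counts.

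For the p-value, the finding is that the permutation set is inconsistent. Distortion is severe under one reading, mostly small under another and absent under the third. The simulated rates depend on the assumed SDs.

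A reader might also point to the newly ART-eligible patients in Section 1 as a secular push. The text gives no date or time course for that change, so it does not establish a trend over the data window, and this point does not rely on it.

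**What to change.** 1. Name as primary the intervention coefficient from a model with fixed effects for site (3) and calendar quarter (14) and a random intercept for TP. Show the crude difference as descriptive only.
2. Use the same coefficient as the permutation statistic.
3. Define the permutation set from the actual randomisation: three sites, with Karaganda and Temirtau moving together. State its smallest attainable p-value: 1/6 one-sided, 1/3 after doubling. Since .05 cannot be reached, say that a permutation p-value cannot alone support a claim of effectiveness, and state the assumptions behind the model-based interval.

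The change is SAP wording and a few model terms. The statistical cost is real: an SE about 2.1 times that of a model with site effects only, at equal residual variance. Separation of effect from time rests on quarters 4 to 7. The period terms do not create concurrent controls for the other 21 post site-quarters; that limit belongs to the design and should be reported with the result.

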examination of the population-level effect in the statistical models to make inferences about the treatment effect.

Power analyses for Aims 1 and 2: Estimates of power to detect significant differences for each hypothesis was conducted. Power analyses were conducted using G\*Power (v3.1.0), two-tailed hypothesis testing, and  $\alpha=.05$ ; results are presented separately for site level data (Figure 3). For site level data, the smallest effect size for Aims 1 and 2 proportion achieving undetectable viral load; power analyses for this “rate limiting” effect size used unconditional exact test to simulate permutation testing method of estimating p-values as well as simulated cluster permutation (i.e., TPs in a city covary together). The autocorrelation and clustering effects were modeled as overall “intraclass correlation” (ICC), using a range of ICCs observed in our prior studies. Results indicate 80% power is achieved with a sample size of 24 TPs (Figure 4).

[figure not shown]

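### The plan names no deciding test and gives the sandwich variance no cluster level or small-sample correction, although only three sites are randomised

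*Combined protocol and SAP*

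**What the plan says.** Under Formal hypothesis testing in the Data Analysis Plan for Primary Study Aim, the first paragraph chooses permutation tests "for significance testing because of concerns that the distribution of measures may not be approximated well by a small sample size". The closing paragraph of the same section then says that hypothesis testing will rest on GLMM and GEE. On the choice between them it says: "The exact choice will be informed by the results from analyses that shed insight into the extent that various assumptions hold or are violated", giving attrition analyses and model fit as examples. On variance it says: "In either case, sandwich estimators for variance will be used which are robust to misspecification of the correlation structure". That paragraph recognises two sources of correlation, repeated measures on one trust point (NSP) and trust points sharing a city. It gives no cluster level for the sandwich, no small-sample correction, no degrees of freedom and no quarter effects.

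Section 2.2 sets the number of randomised units. Software will "sequentially randomly assign the three sites six months prior to implementing BRIDGE in months 22, 28 and 34", and "The unit under experimental control will be a city", with Karaganda and Temirtau combined. Section 2.4 repeats the permutation plan. It also says that inference on the treatment effect will use the population-level effect from the statistical models.

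**The concern.** A sandwich variance is a large-sample device: it needs many independent clusters. Here all eight trust points in a site switch on the same day and share local conditions, so the independent randomised units number three. The plan leaves open how the sandwich treats this, and each available reading has a problem. Clustering on sites or cities respects the shared variation but leaves three or four contributions from which to estimate a variance. Clustering on 24 trust points gives more contributions but treats trust points in one site as independent.

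The plan already doubts distributional approximations at this sample size, yet two paragraphs later it brings in a large-sample variance without saying which p-value governs. The stake is a primary claim resting on a standard error that may be about half its true size.

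**Working it through.** **1. The plan's own figures.** Quarterly data over 42 months give 42/3 = 14 time points. Section 2.4 states 38,416 clustered permutations, and 14^4 = 38,416 exactly (14^3 = 2,744). The count therefore matches four cities that could each start in any of 14 quarters. The randomisation in Section 2.2, three sites to three start dates, has 3! = 6 orders, so a test over the actual assignments has a smallest p of 1/6 = 0.167. Section 2.4 also says "Results indicate 80% power is achieved with a sample size of 24 TPs", "using a range of ICCs observed in our prior studies"; the effect size and ICC values are not in the text, so the power figure cannot be reproduced. Nothing below depends on it.

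**2. Design inputs from the documents.** Three sites of 8 trust points (Section 3.7); 14 quarters (Section 2.4); data collection from month 13 (Appendix A) and roll-out at months 22, 28 and 34, giving (22−13)/3 = 3, (28−13)/3 = 5 and (34−13)/3 = 7 pre-implementation quarters; α = 0.05, "two-tailed hypothesis testing" (Section 2.4).

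**3. Assumed inputs.** The documents give no variance components. For a Gaussian outcome: trust-point variance 0.30, site variance 0.05, residual variance 0.65 with lag-1 correlation 0.5, and a shared site-by-quarter variance varied from 0 to 0.10. For a Poisson outcome: shared site-by-quarter log-SD of 0, 0.1 and 0.2. No treatment effect. Start order is random.

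**4. Type I error of the uncorrected sandwich.** The test is |estimate|/SE > 1.96, with quarter effects in the model. Gaussian: 3,000 runs per scenario. Poisson GEE: 300 runs.

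| Sandwich clustered on | Gaussian | Mean SE / true SD (Gaussian) | Poisson |
|---|---|---|---|
| 3 sites | 40–41% | 0.46–0.48 | 50–52% |
| 4 cities | 33–36% | 0.51–0.56 | 40–49% |
| 24 trust points, no shared variation | 7–8% | – | 8% |
| 24 trust points, shared variation (variance 0.02–0.10; log-SD 0.1–0.2) | 9–21% | 0.64–0.78 for variance 0.05–0.10 | 31–41% |

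Without quarter effects the Gaussian rates are 24–27% on sites and 20–25% on cities. Monte Carlo error is √(0.40×0.60/3000) = 0.9 points at 40% in the Gaussian runs and √(0.5×0.5/300) = 2.9 points in the Poisson runs.

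The standard errors explain most of this. If the SE is a fraction r of the true SD, and its own variability is ignored, the rejection rate is 2[1 − Φ(1.96r)]:
- r = 0.47: 1.96×0.47 = 0.92, giving 36%
- r = 0.53: 1.96×0.53 = 1.04, giving 30%
- r = 0.65: 1.96×0.65 = 1.27, giving 20%

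The remaining gap at site and city level reflects the variability of an SE built from three or four pieces.

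A second simulation with the same layout, a trust-point-by-quarter SD of 1 and an assumed shared shock SD of 0.3 gave 39–41% on sites. On trust points it gave 7% without shocks and 16–19% with them.

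**5. Effect of the open model choice.** Always taking the smaller p from two working correlation structures, a stand-in for choosing between GEE and GLMM, moved the rate from 41% to 43% on sites and from 8.1% to 8.6% on trust points: about 2 points at most. A full GLMM was not fitted.

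**6. Candidate remedies (Gaussian, quarter effects).**
- t reference on G−1 df without correcting the sandwich: 14–19% on sites or cities.
- Mancl–DeRouen-type correction on 24 trust points, t(23): 5% with no shared variation, 10–16% at shared variance 0.05–0.10.
- The same correction on 3 sites: 7–8% with z, about 2% with t(2).
- Two-way fixed-effects test on site-quarter means, df = 42 − 3 − 13 − 1 = 25: about 5% without serial correlation, 8% when only the shared shocks are autocorrelated (0.7), and 12–15% when trust-point residuals are autocorrelated at 0.5–0.7.

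**The case against.** The strongest reply is that the plan gives significance testing to permutation, both in Section 2.4 and in the Data Analysis Plan, so the model is there for estimation and its p-value decides nothing. The comparison is also set at trust-point level, which makes 24 clusters the natural reading; there the error is 7–8% unless sites share quarter-to-quarter shocks of a size the documents never state.

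Much of this stands. The inflation reaches the trial's conclusion only where a model p-value or interval is used, and the trust-point figures above 8% rest on an assumption. It does not dispose of the point. The closing paragraph expressly puts hypothesis testing on the models, Section 2.4 draws inference from the model effect, and no interval is described for the permutation test, so any reported interval would carry the sandwich SE. The rule in Section 2.4 for reporting the more conservative p-value compares two permutation schemes and does not cover the model. Shared shocks are plausible: Section 2.2 itself cites budget reductions and newly launched HIV programmes as time-specific influences.

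A reader might infer that the error is several times nominal however the sandwich is clustered. The documents do not support that, because the cluster level is unstated and the trust-point result depends on unstated shared variation. A reader might also infer that choosing GLMM or GEE after seeing data drives the inflation. The choice is tied to assumption checks rather than to treatment-effect results, and even the worst-case stand-in adds only about 2 points.

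**Conclusion.** The point holds in conditional form. The plan does not say which test decides, and it specifies a sandwich variance without cluster level, correction or degrees of freedom for three randomised units. None of the uncorrected versions examined holds 5%. The rate is about 40% on sites and 33–36% on cities (Gaussian), and this hardly depends on the assumed shared variation. On trust points it is 7–8% without shared variation and about 9–21% with the assumed Gaussian amounts. The Poisson figures are higher but come from 300 runs and should be read as indicative. The GLMM/GEE choice is a minor pre-specification weakness.

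It would go too far to conclude that the trial's result will be wrong. That depends on the model p-value or interval being the one relied on. Nor is the permutation test a ready safeguard: its stated reference set does not match the randomisation, and the matching set of six orders cannot reach 0.05.

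**What to change.** Before analysis, reconcile the two paragraphs of the Data Analysis Plan (and Section 2.4) by naming one deciding test and giving the other a stated supporting role. Do not use the uncorrected sandwich. For the model:

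- fix GLMM or GEE in advance, with a stated fallback for non-convergence;
- include quarter effects;
- account for shared site-by-quarter variation and for serial correlation within trust point and within site;
- base p-values and intervals on a small-sample method at the level of the randomised unit, for example a bias-corrected (Mancl–DeRouen-type) site-level sandwich with a t(2) reference. This held about 2% in the Gaussian simulation and should be checked for the planned count and binary outcomes.

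A site-quarter model with an explicit autocorrelation structure and matching degrees of freedom is an alternative if its type I error is first shown by simulation. The plain 25-df test on cell means should not be presented as holding 5%.

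The plan should also state openly the limit that three randomised units set on any test. The cost is SAP wording, a modest simulation, wider intervals and lower power; the t(2) option is conservative.
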